### Interim Analysis and Stopping Rule

A data and safety monitoring board (DSMB) consisting of members who are not involved in the study and have expertise in clinical aspects of the illnesses, surgery, study patient population, clinical trial conduction, methodology, and biostatistics will analyse the data of all enrolled subjects after enrolment of each of the 40 study patients. A DSMB will have the full authority to determine the need to terminate this study early. The stopping rule will take effect if the mean value of minimal PaO_2_/FiO_2_ (primary outcome) in restrictive oxygenation group is clinically concerning lower (PaO_2_/FiO_2_ < 150 mmHg for 2 consecutive measurement periods). There will be 4 review periods for each of the 40 new patients after the completion of the data collection period.

### Statistical Analysis

#### Sample Size Calculation

A decrease of 10% in PaO_2_/FiO_2_ from the baseline is considered as clinically significant. The ARDS definition is PaO_2_/FiO_2_ less than 300 mmHg; thus, a difference of 30 mmHg of mean value of the lowest PaO_2_/FiO_2_ postoperatively between the 2 groups will be considered as clinically significant. Assuming SD of 60 mmHg, *α* = 0.05, and 80% power with 2-sided *t*-test, at least 160 subjects will be needed in total to detect a difference (80 patients in each group). Considering potential withdrawal, protocol violation, and failure to follow-up, we will aim to recruit 200 patients (100 patients in each group) for this study.

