## Methods

### Study Design and Setting

This study is a prospective, observer-blinded, web-based centrally randomised, controlled, multicentre, international clinical trial to assess the relationship between intraoperative FiO_2_ and PPCs. Surgical technique will be restricted to CABG with CPB through median sternotomy to minimise variation. Arterial partial pressure of oxygen/FiO_2_ will be assessed at baseline (preoperative values), time of postoperative ICU admission as well as 4 hours, 8 hours, 12 hours, 18 hours, 24 hours, 36 hours, and 48 hours after postoperative ICU admission (Figure 1). The study will be conducted at University of Louisville Health, Louisville, KY, USA, and 5 teaching hospitals from China with a combined more than 8000 open-heart surgeries and over 1000 CABG with CPB cases per year. We have been assured fair access to research subjects to enable completion of this study within a 1-year period. Written informed consent will be obtained from each participant preoperatively.

This study is designed not to interfere with routine clinical workflow, and patients will be centrally randomised to either restrictive or liberal oxygenation groups in a 1 : 1 ratio, and the randomisation will be stratified for each centre. For blinding, the research fellows and ICU physicians who record and assess the primary and secondary outcomes as well as who manages the patients will be blinded to the randomisation group assignment. The principal investigator (PI) of each centre and the physicians who conduct the anaesthesia and monitoring intraoperatively in the operating room are unblinded due to necessary requirements for clinical care. This protocol is in accordance with the Recommendations for Interventional Trials (SPIRIT) checklist. The SPIRIT figure demonstrates the schedule of enrolment, interventions, and outcome assessment of this trial (Table 1).

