### Data Analysis

Data will be expressed as mean ± SD or median (minimum and maximum) and percentage as appropriate for continuous and categorical variables, respectively. A *t-*test will be used to compare continuous variables. For comparison of ratio or ordinal categorical data, the Pearson chi-squared test (or Fisher’s exact) or a Mann–Whitney *U*-test will be used. Two-sided *P-*values less than .05 will be considered statistically significant. All the analyses will be conducted using the R software.

The primary outcome of the study is the lowest PaO_2_/FiO_2_ within 48 hours after ICU admission between liberal and restrictive oxygenation groups. A non-parametric equivalent *t-*test will be used to compare groups. The percentage of shift from baseline will also be calculated and compared by the *t-*test. The ratio of shift over 10% from the baseline of each group will be compared by the chi-squared test. Secondary outcome analysis of PPC incidence and mortality of the groups will be compared by the chi-squared test. Odds ratios or measures of relative risk will include 95% CIs. Secondary outcomes including the length of mechanical ventilation and lengths of postoperative ICU and hospital stay will be calculated and compared by a *t-*test.

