The major limitation of this study lies in the difficulty of balancing many confounding factors during CABG with CPB that are harmful to the lungs, including the surgical procedure, CPB, hypothermia, blood contact with artificial surfaces, ischaemia–reperfusion injury, administration of blood products, and lung collapse.^21^ In our protocol, if the patient develops haemodynamic instability which requires a return to CPB or suffers circulatory arrest, they will be withdrawn from the study. We will also withdraw patients who require mechanical circulatory support systems like extracorporeal membrane oxygenation, ventricular assist device, or an Impella device for similar reasons. Transfusion is common in cardiac surgery, but CABG has a relatively low transfusion rate compared to other open-heart surgeries.^22^ Transfusion-associated lung injury (TRALI) has been well defined, and it is a prominent factor for increased morbidity and mortality.^23,24^ The reported incidence of TRALI varies widely, ranging from 0.0008% to 1.2% per unit of blood product administered and from 0.08% to 8% per transfused patient.^25^ Since transfusion of blood products, in particular blood plasma, may cause lung injury, these patients will also be withdrawn from our analysis. We predict a high rate of withdrawal, not only for safety reasons but also for bias control and balancing of confounding factors. Another study limitation is our inability to blind the anaesthesiologist. Only ICU physicians and research fellows/study coordinators who assess the outcomes will be blinded.

There exists increasing evidence that a restrictive oxygenation strategy may be beneficial in various groups of patients.^26^ It is important to understand the relationship between FiO_2_ and lung injury after cardiac surgery. This is one of the first randomised controlled trials to prospectively evaluate the influence of high inspired oxygen concentrations on pulmonary outcomes and oxygenation after cardiac surgery.

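### The stated sample size inputs give 128 patients for 80% power, not the printed minimum of 160; the error is conservative, but the figure needs correcting or its missing input stating

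*Protocol article*

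**What the plan says.** The Sample Size Calculation section of the protocol article gives all the ingredients together. The target is "a difference of 30 mmHg of mean value of the lowest PaO_2_/FiO_2_ postoperatively between the 2 groups". The variability is given as "Assuming SD of 60 mmHg". The section sets alpha at 0.05 "and 80% power with 2-sided *t*-test". It concludes that "at least 160 subjects will be needed in total to detect a difference (80 patients in each group". Only after that does it allow for withdrawal, protocol violation and loss to follow-up, raising the target to 200 (100 per group). No attrition rate is given.

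Three other places bear on the point:

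- Study Design and Setting fixes equal allocation: "patients will be centrally randomised to either restrictive or liberal oxygenation groups in a 1 : 1 ratio".
- Data Analysis keeps the two-sided 5% level, but plans a non-parametric comparison for the primary outcome rather than the t-test used for sizing.
- The Discussion says "We predict a high rate of withdrawal".

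**The concern.** A standardised difference of 30/60 = 0.5 at two-sided 5% and 80% power is a familiar case, and its answer is well below 80 per group. All the inputs and the result are printed together, so the mismatch is not a matter of detail left to a fuller document.

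Two things are at stake.

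- **Attrition.** The stated minimum is what a sponsor, ethics board or monitoring board would use to judge how much loss the trial can bear, and the authors expect much. Read as printed, the trial drops below its stated power once more than 40 of 200 patients (20%) are lost. On the printed inputs that is not so.
- **A hidden assumption.** If 160 came from a larger SD or a smaller difference, then a printed input is wrong and the real margin is smaller than those inputs imply. A reader cannot tell which.

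**Working it through.** **Inputs.** Difference 30 mmHg, SD 60 mmHg, alpha 0.05, power 80%, two-sided t-test (Sample Size Calculation); 1:1 allocation (Study Design and Setting). Standardised difference d = 30/60 = 0.5.

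**Step 1: try to reproduce 80 per group.**

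Normal approximation: n per group = 2 × (z₀.₉₇₅ + z₀.₈₀)² / d² = 2 × (1.960 + 0.842)² / 0.25 ≈ 62.8, so 63 per group (126 in total).

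Exact calculation (noncentral t): n = 63.77, so 64 per group (128 in total), with power 80.1%.

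The printed figure is not reproduced: 160/128 = 1.25, which is 25% too high. The two methods differ by only one patient per group, so the choice of formula does not explain the gap.

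**Step 2: power at the printed sizes.**

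Normal approximation at 80 per group: 0.5 × √(80/2) − 1.960 = 3.162 − 1.960 = 1.202, and Φ(1.202) = 0.885. Exact t-test values:

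| Per group | Total | Power |
|---|---|---|
| 64 | 128 | 80.1% |
| 80 | 160 | 88.2% |
| 100 | 200 | 94.0% |

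**Step 3: does another test, power or alpha give 80 per group?** All at d = 0.5; exact results rounded up.

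| Variant | Per group |
|---|---|
| One-sided, 80% power | 51 |
| One-sided, 90% power | 70 |
| Two-sided, 85% power | 73 |
| Two-sided, 88% power | 80 |
| Two-sided, 90% power | 86 |
| Two-sided alpha 0.025, 80% power | 78 |
| Two-sided alpha 0.0125, 80% power | 91 |
| Mann–Whitney, efficiency 0.955: 63.77/0.955 = 66.8 | 67 |
| Mann–Whitney, worst-case efficiency 0.864: 63.77/0.864 = 73.8 | 74 |

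Only a power of about 88% reaches 80, and the text says 80%.

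**Step 4: what else would give 160?** With 80 per group and 80% power the detectable standardised difference is 0.446. That corresponds to an SD of 30/0.446 ≈ 67 mmHg, or to a difference of 0.446 × 60 ≈ 27 mmHg. Alternatively, 128/(1 − 0.20) = 160 exactly, and 160/(1 − 0.20) = 200 exactly, which is the pattern that a 20% attrition allowance applied twice would leave.

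**Step 5: loss from 200 before power falls below 80%.**

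| Basis | Needed in total | Tolerable loss |
|---|---|---|
| As printed | 160 | 40/200 = 20% |
| t-test, stated inputs | 128 | 72/200 = 36% |
| Non-parametric, efficiency 0.955 | 134 | 66/200 = 33% |
| Non-parametric, worst case 0.864 | 148 | 52/200 = 26% |

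For the non-parametric test at 80 per group, the effective size is 80 × 0.955 = 76.4 or 80 × 0.864 = 69.1 per group, and power is 86.7% or 83.1%.

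**The case against.** The best defence is that 160 already contains a 20% allowance for attrition. The arithmetic fits exactly, so it would be wrong to say that no natural route leads to 160. It remains an inference: no rate is stated, and the section presents 160 as the number needed to detect the difference, adding losses only afterwards. If this is what happened, the sentence is still wrong as written, because the allowance has been counted twice.

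A second defence is that 160 allows for the non-parametric primary test. The section names the t-test, and the non-parametric requirement is 134 to 148. The objection does limit the claim, though: 128, 88% and 36% are t-test figures, and the planned primary comparison has a somewhat smaller margin.

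A third is that the interim reviews required a larger sample. The sizing text mentions no such adjustment, and Interim Analysis and Stopping Rule describes stopping for low PaO2/FiO2 in the restrictive group, not repeated tests for efficacy.

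Finally, the error is on the safe side and changes neither enrolment nor the analysis. That stands, and it sets the weight of the point. A reader might infer from a wrong sample size that the trial is too small; on the stated inputs the opposite holds. A reader might also take 36% as an acceptable level of loss. The documents do not support that either. Withdrawals under Safety Assessment and Table 2 occur after randomisation, and one Table 2 criterion applies to the restrictive group only, so bias is a separate risk that a power margin does not measure.

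**Conclusion.** The point holds as a conservative arithmetic error. The stated inputs need 128 patients, not 160; at 160 the t-test has about 88% power, and at 200 with no losses 94%. The stated alpha, power and test do not yield 160. The unstated explanations that fit are about 88% power, an SD of about 67 mmHg, a difference of about 27 mmHg, or a 20% attrition allowance already included, and the document does not let a reader choose between them.

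The t-test figures assume equal groups, a common SD of 60 mmHg and a true difference of 30 mmHg. The non-parametric range (134 to 148 needed; about 83% to 87% power at 160) assumes a Mann–Whitney comparison with efficiency between 0.864 and 0.955. All loss margins concern power only. The correction should be made because the plan's stated size and power disagree with its own inputs, not because the trial's adequacy on those inputs is in doubt.

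**What to change.** Keep enrolment at 200 and make one of two corrections in Sample Size Calculation.

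- **If the printed inputs are right:** state that 64 per group (128 in total) give 80% power by two-sided t-test, that the non-parametric primary test needs about 134 to 148 in total, and that 160 analysed patients give about 88% power by t-test (about 83% to 87% non-parametric).
- **If 160 came from something else:** state that input, whether power, SD, difference or attrition already counted.

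In either case give the attrition rate that leads to 200. The cost is a sentence or two, with no change to enrolment, data collection or analysis. Study Registration says recruitment had not begun, so the correction can be made before the first patient.

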### Data Analysis

Data will be expressed as mean ± SD or median (minimum and maximum) and percentage as appropriate for continuous and categorical variables, respectively. A *t-*test will be used to compare continuous variables. For comparison of ratio or ordinal categorical data, the Pearson chi-squared test (or Fisher’s exact) or a Mann–Whitney *U*-test will be used. Two-sided *P-*values less than .05 will be considered statistically significant. All the analyses will be conducted using the R software.

The primary outcome of the study is the lowest PaO_2_/FiO_2_ within 48 hours after ICU admission between liberal and restrictive oxygenation groups. A non-parametric equivalent *t-*test will be used to compare groups. The percentage of shift from baseline will also be calculated and compared by the *t-*test. The ratio of shift over 10% from the baseline of each group will be compared by the chi-squared test. Secondary outcome analysis of PPC incidence and mortality of the groups will be compared by the chi-squared test. Odds ratios or measures of relative risk will include 95% CIs. Secondary outcomes including the length of mechanical ventilation and lengths of postoperative ICU and hospital stay will be calculated and compared by a *t-*test.

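### The primary analysis is an unnamed, unadjusted non-parametric test that does not estimate the 30 mmHg mean difference on which the trial is sized, and it leaves baseline and centre unused

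*Protocol article*

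**What the plan says.** All references are to the protocol article.

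- **Sample Size Calculation.** The target is a difference in means: "a difference of 30 mmHg of mean value of the lowest PaO_2_/FiO_2_ postoperatively between the 2 groups will be considered as clinically significant". The calculation is set up with "Assuming SD of 60 mmHg", a two-sided alpha of 0.05 and "80% power with 2-sided *t*-test". It gives 160 patients (80 per group), raised to 200 for losses.
- **Data Analysis, general rule.** A t-"test will be used to compare continuous variables". The Mann-Whitney U-test is named only in the sentence on ratio or ordinal categorical data.
- **Data Analysis, primary outcome.** "A non-parametric equivalent *t-*test will be used to compare groups". The sentence names no test, covariate or stratum.
- **Data Analysis, use of baseline.** "The percentage of shift from baseline will also be calculated and compared by the" t-test, and the proportions with a shift above 10% are compared by chi-squared. Confidence intervals are promised only for odds ratios and relative risks.
- **Study Design and Setting.** PaO2/FiO2 "will be assessed at baseline (preoperative values"), and "the randomisation will be stratified for each centre". There are six hospitals, one in the USA and five in China.

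**The concern.** The trial declares in mmHg what matters clinically and sizes itself on that quantity. It then fixes a primary test whose natural result is a P value about ranks. Non-parametric equivalent of a t-test could mean Mann-Whitney or a permutation test, and these do not address the same quantity. If Mann-Whitney is meant, the report could show a significant or non-significant result with no planned estimate and interval to compare with 30 mmHg.

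The comparison is also fixed without adjustment, although two useful variables are already in hand. Baseline PaO2/FiO2 is measured before surgery but enters only through percentage shift and a dichotomy at 10%, which are generally less efficient than using baseline as a covariate. Centre defines the randomisation strata, and an analysis that ignores it tends to overstate the standard error if centres differ.

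**Working it through.** **Inputs from the document:** difference 30 mmHg, SD 60 mmHg, two-sided alpha 0.05, power 80%, t-test, 80 evaluable per group.

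**Inputs assumed, because the document gives neither:** correlation r between baseline and nadir PaO2/FiO2, 0.2 to 0.5; share of outcome variance lying between centres (ICC), 0.05 to 0.10.

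**1. The plan's own figure.** n per group = 2(1.960 + 0.842)² × 60²/30² = 2 × 7.85 × 4 = 62.8, so 63 per group and 126 in total. The exact t-test calculation gives 63.8, so 64 per group and 128 in total. The stated 160 is therefore not reproduced. Of the variants tried, only 128/(1 − 0.20) = 160 matches, which would mean that 160 already contains a 20% allowance. That is a separate matter. For this point it means only that 160 leaves a margin.

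**2. Does the rank test endanger power?** At 80 per group:

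| Test | Basis | Power |
|---|---|---|
| t-test | exact | 88.2% |
| t-test | normal approximation | 88.5% |
| Mann-Whitney, normal data | efficiency 3/π, effective n = 80 × 0.955 = 76.4 | 87.1% |
| Mann-Whitney, normal data | simulation, 10,000 replicates | 86.5% |
| Mann-Whitney, lower-bound efficiency | 0.864, effective n = 69.1 | 83.6% |

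All exceed 80%. With only 64 evaluable per group (128 of 200, a 36% loss), the simulation gives 80.5% for the t-test and 78.2% for Mann-Whitney.

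**3. Precision from baseline.** Residual SD = 60√(1 − r²). The 95% half-width at 80 per group is 1.96 × SD × √(2/80). The comparator is the unadjusted t-test.

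| r | Residual SD (mmHg) | Half-width (mmHg) | Narrower by | Power (normal approx.) |
|---|---|---|---|---|
| 0 | 60.0 | 18.6 | – | 88.5% |
| 0.2 | 58.8 | 18.2 | 2% | 89.8% |
| 0.3 | 57.2 | 17.7 | 5% | 91.2% |
| 0.5 | 52.0 | 16.1 | 13% | 95.5% |

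**4. Cost of ignoring centre.** If arms are balanced within centre, the unadjusted standard error is too large by a factor 1/√(1 − ICC).

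- ICC 0.05: 1/√0.95 = 1.026. The true size of a nominal 5% test is 2[1 − Φ(1.96 × 1.026)] = 4.4%.
- ICC 0.10: 1/√0.90 = 1.054. The true size is 3.9%.

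The error is on the conservative side.

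**5. Price of adjusting.** One baseline term and five centre terms reduce the residual degrees of freedom from 158 to 152 at 160 patients, which is negligible.

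**The case against.** **The specific sentence governs.** The t-test sentence is a general rule and the primary outcome then receives its own sentence. A reader might infer that the protocol offers two rival primary tests, so that the P value depends on which is followed. The document does not support this: on an ordinary reading the primary-outcome sentence prevails. What stands is that the test it prescribes is unnamed and does not match the quantity used for sizing.

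**Sizing with a t-test and analysing with its rank counterpart is common and does no harm here.** As to power, this is right. A reader might infer an underpowered trial, but at 160 evaluable patients step 2 shows otherwise. The reservation is that the Discussion predicts a high withdrawal rate, so 160 is not assured.

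**One primary outcome, not three.** A reader might infer that the primary outcome is tested three times at 0.05: nadir, percentage shift and shift above 10%. The article consistently names only the nadir as primary and introduces the percentage shift as an additional calculation. A multiplicity charge is not supported. A label calling the shift analyses supportive would still help.

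**Adjustment belongs in the statistical analysis plan, and an unadjusted randomised comparison is valid.** Both are fair, and nothing in the article forbids an adjusted analysis. The point here is not missing detail, however: the article itself states the primary test, and the one it states is unadjusted.

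**The gain rests on assumed inputs.** This stands. A low correlation is plausible: baseline is taken on room air, the nadir follows bypass, and eligibility narrows the baseline range by excluding severe COPD and preoperative oxygen. The standard-error figure also needs balance within centre, and the article mentions stratification but no blocking.

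**An estimate could be derived from the reported means and SDs.** It could, if means are reported. The same sentence allows median with minimum and maximum instead, and these would not yield it.

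**Conclusion.** The concern holds as an improvement that is nearly free, not as an error that invalidates the trial. Two parts rest on the text alone: the primary test is unnamed, and, read as a rank test, it does not estimate the mean difference that the protocol calls clinically significant, for which no interval is specified.

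The third part, precision given up by omitting baseline and centre, has a known direction but an unknown size. On the stated assumptions, baseline adjustment is worth a 2 to 13% narrower interval, and centre accounts for a standard error about 3 to 5% too large. The centre effect makes the test conservative, so false positives are not inflated. Power is adequate under either test if 160 patients are evaluable.

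**What to change.** Replace the primary-outcome sentence in Data Analysis with one named analysis: a linear model (ANCOVA) of the lowest PaO2/FiO2 on group, baseline PaO2/FiO2 and centre, reporting the adjusted mean difference in mmHg with its 95% confidence interval and one two-sided P value. Keep a centre-stratified rank test (van Elteren) as a sensitivity analysis, which preserves the protection against skewed data that the non-parametric wording presumably sought. State that the percentage-shift and above-10% comparisons are supportive.

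The cost is wording in the protocol and the statistical analysis plan. All the variables are already collected and no extra patients are needed. The article states that recruitment has not begun, so the change can be made before any data are seen.
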